### Study Design

#### Recruitment

The SPIRIT guidelines were used in the construction of this manuscript (Checklist 1)*.* The participant process flow diagram (Figure 1) outlines the study process. Eligible volunteers will be recruited through NHS Scotland’s Primary Care clinical database. Those who qualify will receive a recruitment pack that contains a recruitment letter, participant information sheet, and consent form and will have 2 weeks to review the materials, discuss the study with an independent researcher, and decide whether they wish to participate. Following this period, a follow-up telephone call will be made to confirm the receipt of the recruitment pack and to determine if the individual is interested in joining the study.

Individuals expressing interest will be asked to provide signed consent and will be invited to a screening visit, which can take place either at the surgery or in their home. During this visit, the study will be explained in detail, and any additional questions will be addressed. Participants will have the opportunity to view and test the wearable device, as well as learn how to use the accompanying app, with support from the research team to set up the device and initiate their participation in the study.

Participants will have the freedom to withdraw from the study at any time and for any reason without any impact on their care and without the obligation to provide a reason for their withdrawal.

**Figure 1. F1:**
[figure not shown]
Participant process flow diagram.

#### Participant Training

Each participant will be provided with the necessary equipment, including the Frontier X2 device, battery charging materials, cleaning products, and a detailed instruction manual. Participants will also be required to download the Frontier X2 app onto a suitable smartphone, and they will be creating an account using their designated study code and email. For participants who do not own a smartphone, one will be supplied by the research team. Similarly, those without a stable Wi-Fi connection will receive a SIM card to enable cellular data access.

Throughout the participation period, participants will receive guidance on how to properly use and maintain the device, which includes instructions on the following:

Device usage: How to wear and operate the Frontier X2.Data collection: Procedures for syncing data with the app.Charging protocols: Ensuring the device remains functional throughout the study.Light signals: Understanding the various light patterns emitted by the device, which indicate its status.

#### Patient Population Size

The study will recruit a total of 30 volunteers, all of whom have been diagnosed with COPD and have experienced at least one exacerbation, resulting in hospitalization within the 12 months prior to enrollment. This inclusion criterion increases the likelihood that participants will experience an additional exacerbation during the 18-month follow-up period.

According to a previous study [27], it has been found that COPD exacerbation rates range from 0.5 to 3 events per person per year. Over an 18-month period, this corresponds to an expected 0.75 to 4.5 exacerbations per individual. While only the first exacerbation is relevant to the primary end point of this study, this range suggests that a large proportion of participants—potentially 70% or more—are likely to experience at least one exacerbation within the study timeframe. Therefore, a sample size of 30 participants is expected to yield a sufficient number of exacerbation events for retrospective physiological signal analysis, while accounting for variability in exacerbation frequency and potential loss to follow-up.

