## Results

Following ethical approval of the study protocol, the first patient was enrolled in June 2024, and recruitment was completed in July 2025. Data collection is ongoing and is expected to be completed by December 2025, within the planned 18-month study period. Statistical analysis is being conducted simultaneously with data collection. Final results are expected to be submitted for publication in January 2026. The findings, regardless of whether they are positive or negative, will be disseminated through peer-reviewed journals.

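### The event yield that justifies 30 participants gives everyone 18 months of follow-up, but the study calendar allows about 5 to 18 months, and 70% is not a floor over the stated rate range

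*Protocol article*

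**What the plan says.** The Patient Population Size section of the protocol article sets the size: "The study will recruit a total of 30 volunteers". It argues that a recent hospitalised exacerbation makes it more likely that "participants will experience an additional exacerbation during the 18-month follow-up period". From a cited study it takes that "COPD exacerbation rates range from 0.5 to 3 events per person per year", and over 18 months "this corresponds to an expected 0.75 to 4.5 exacerbations per individual". It notes that only the first exacerbation matters for the primary end point, and says that the range suggests that a large proportion, "potentially 70% or more—are likely to experience at least one exacerbation within the study timeframe". It concludes that 30 is enough, "while accounting for variability in exacerbation frequency and potential loss to follow-up".

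The Results section gives the calendar: "the first patient was enrolled in June 2024, and recruitment was completed in July 2025". It continues: "Data collection is ongoing and is expected to be completed by December 2025, within the planned 18-month study period". The Results paragraph of the Abstract agrees, placing the end of data collection within 18 months of study initiation. The Methods paragraph of the Abstract says that each participant wears the device for at most 18 months, or until an exacerbation.

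**The concern.** The conversion from a yearly rate to 0.75 to 4.5 events per person is right only if every participant can be observed for 18 months. On the stated dates, 18 months runs from the first enrolment to the end of collection, so only the earliest entrants can reach it.

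The step from 0.75 to 4.5 expected events to 70% or more with at least one event is a separate matter. A mean of 0.75 events does not put 70% of people above zero.

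The number of first events matters because the Quantitative Analysis section makes sensitivity an explicit performance measure of the CUSUM chart, and confirmed exacerbations are its denominator. The event yield is also the only argument the article gives for 30 participants.

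**Working it through.** **Inputs.** From Patient Population Size: n = 30, rate r = 0.5 to 3 per person-year, 18 months (1.5 years) for each participant, 70% or more with a first event (0.70 × 30 = 21), and no figure for loss. From Results: first enrolment June 2024, last July 2025, end of collection December 2025.

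**Plan's own figures.** 0.5 × 1.5 = 0.75 and 3 × 1.5 = 4.5, so the expected events per person reproduce. The 70% does not follow from the whole range, as shown below.

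**Follow-up on the calendar.** June 2024 to December 2025 is about 18 months; July 2025 to December 2025 is about 5 months. Potential follow-up therefore runs from about 5 to 18 months. This step needs no model.

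**Share with at least one event, 18 months for all.** With a constant rate, P = 1 − exp(−1.5r). At r = 0.5, P = 1 − exp(−0.75) = 52.8%, or 15.8 of 30. Solving P = 0.70 gives r = −ln(0.30)/1.5 = 0.80 per year.

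**Share on the calendar.** The article gives only the first and last entry dates, so I assume uniform entry, with follow-up spread evenly from a = 5/12 to b = 18/12 years. Then P = 1 − [exp(−ra) − exp(−rb)] / [r(b − a)]. At r = 0.5 this is 1 − (0.8119 − 0.4724)/(0.5 × 1.0833) = 37.3%.

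| Rate per year | 18 months for all | 5–18 months, uniform entry | Expected of 30 (calendar) |
|---|---|---|---|
| 0.5 | 53% | 37% | 11.2 |
| 0.8 | 70% | 52% | 15.6 |
| 1.0 | 78% | 60% | 17.9 |
| 1.75 (midpoint) | 93% | 78% | 23.5 |
| 3.0 | 99% | 92% | 27.5 |

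On the calendar, 70% is reached at about 1.35 per year.

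**Sensitivity to the assumptions, at 0.5 per year.** Moving the ends of the calendar by a month gives 36% to 40%. A single mean follow-up anywhere from 8 to 15 months gives 28% to 47%. Letting rates differ between people (gamma-Poisson) lowers the 18-month figure from 53% to 47% at shape 2 and 43% at shape 1.

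**Losses.** The article gives no figure. If 10% to 20% of participants contributed no event (an assumption), the calendar yield at 0.5 per year would be 30 × 0.9 × 0.373 = 10.1 down to 30 × 0.8 × 0.373 = 9.0. At 1.75 per year with 20% lost it would be 30 × 0.8 × 0.784 = 18.8.

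**Precision at these counts.** Exact (Clopper-Pearson) 95% intervals for a sensitivity near 80% (an illustration) are:

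- 9 of 11: 48% to 98%
- 17 of 21: 58% to 95%
- 22 of 27: 62% to 94%

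**The case against.** The text is hedged: it says potentially, and it does not tie 70% to the lowest rate. With 18 months for all, 70% holds from 0.80 per year upward, which is (3 − 0.80)/2.5 = 88% of the stated range. On the calendar it holds from 1.35 per year, (3 − 1.35)/2.5 = 66% of the range. At the midpoint the calendar still gives 78%, and averaging evenly over the range gives 74%. The cohort is also enriched by a hospitalised exacerbation in the previous year, so a rate above the minimum is plausible. All of this stands. A reader might infer that 70% is refuted, or that 37% is what the study will deliver. The documents support neither: 37% belongs to the lowest rate and rests on uniform entry and a constant rate, which the article does not state. Equally, the article gives no rate for the enriched group, so nothing in it establishes a rate of 1.35 or more.

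A reader might also infer that the estimates will be less precise than the article promises. It promises no precision: there is no interval, target width or minimum number of events.

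This is an uncontrolled feasibility study, and Strengths and Limitations concedes that size and duration may be insufficient. That lowers the stakes, but a general caveat does not correct a specific premise that the article's own dates contradict. A numerical loss allowance may sit in a fuller protocol. Even so, the article says that loss was accounted for, and nothing in the calculation it prints reflects any.

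**Conclusion.** The point holds as a correction to the event-yield justification. Three things are wrong as written.

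1. The section gives every participant 18 months, while the stated calendar gives about 5 to 18 months depending on entry date. This rests on the document's dates alone.
2. The 70% is presented as following from a range whose lower end gives 53% even with full follow-up, taking a constant rate. On the calendar, with uniform entry as well, the share runs from about 37% to 92% over the range, and the rate needed for 70% rises from about 0.80 to about 1.35 per year. So 70% is attainable within the range, but it is not a floor.
3. Loss to follow-up is said to be accounted for, with no allowance shown.

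The Abstract's limit of 18 months per participant is consistent with the calendar. No hypothesis test or power statement is affected.

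**What to change.** In Patient Population Size:

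- Replace the 18 months for everyone with the follow-up implied by the entry dates. Recruitment is complete, so these are known and no accrual model is needed.
- State the exacerbation rate assumed and the loss allowance, or delete the claim that loss is accounted for.
- Replace the 70% statement with the expected number of participants with a first event over the full 0.5 to 3 per year. Under uniform entry this is roughly 11 to 27 of 30 before losses; the real entry dates should replace that approximation.
- Give the exact confidence interval for sensitivity at those counts.

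The Abstract's wording on maximum wear time needs no change. The cost is a few sentences and a less favourable stated yield. No extra participants are required.

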#### Study Assessments

A researcher will separately meet each participant every 2 weeks to monitor progress and enquire whether they have experienced any exacerbations that have required medical attention. Two questionnaires will be completed by the participant. A COPD symptom questionnaire is used to assess any changes in the participant’s symptoms as independent variables, including appetite, breathing, cough, energy levels, general wellness, and medication usage. In addition, a Device Usage and Adherence Questionnaire will evaluate the participant’s experience with the Frontier X2 device, focusing on ease of use, adherence to the study protocols, and any challenges they may have faced while using the device. Following the completion of the questionnaires, the researcher will address any technical issues related to the device or app, offer troubleshooting assistance, and answer any questions the participant may have about the study. These visits will ensure regular communication and allow the researcher to provide support, ensuring that participants are comfortable with the device and that any concerns are promptly resolved.

### Study Setting

The primary setting for this study will be remote, real-time home-based monitoring, allowing participants to use the device in their everyday environment. Data will be collected continuously in this real-life setting, ensuring that the study reflects the participants’ typical routines and lifestyle conditions, thereby enhancing the validity of the results.

### Study Participants

#### Inclusion Criteria

The participant must meet all the following criteria to be considered eligible for the study: (1) any person aged 18 years or over, (2) current diagnosis of patients with COPD who have experienced exacerbation-induced hospitalization in the previous year, (3) be willing and able to comply with study procedures and be available for study visits, (4) be able to use a “smartphone, tablet, or computer,” (5) be able to give written consent, and (6) able to understand written and spoken English.

#### Exclusion Criteria

The participant may not enter the study if any of the following applies: (1) the inability to give written informed consent; (2) known respiratory disorders other than COPD which, in the opinion of the investigator, is the main contributor to the patient’s symptoms (eg, asthma, lung cancer, sarcoidosis, other interstitial lung diseases, tuberculosis, lung fibrosis, cystic fibrosis, and non-COPD-related bronchiectasis); (3) a known history of significant systemic and other organ-related diseases, other than COPD, which, in the opinion of the investigator, is likely to interfere with the study or impact on participant safety (eg, severe rheumatoid arthritis and lupus, kidney, liver, endocrine, psychological disorders); (4) known to be severely alpha-1-antitrypsin deficient (PiSZ or PiZZ); (5) any known history of violence/chaotic substance misuse based on their medical records; (6) having undergone lung surgery (eg, lung volume reduction, lobectomy) within the last 6 months; (7) have cancer or other terminal condition which, in the opinion of the investigator, has a mortality of 12 months or less; (8) taking high-dose oral corticosteroid medication (equivalent to a daily dose of ≥10 mg of prednisolone) for more than 3 consecutive months; (9) being pregnant; (10) patients already involved in an ongoing research study; (11) participation in an interventional clinical study within 3 months of Visit 1 or participation in a study using an investigational medicinal product either in the previous 3 months or in the interval from last using the investigational medicinal product to 5 times its half-life; (12) patients with other significant lung disease, unable to consent, unable to use the technology (eg, inability to use the data device or complete the questionnaires), or at the clinician’s discretion for other more significant medical/social reasons; (13) known allergy to any chest strap; (14) on long-term oxygen therapy; and (15) acute exacerbation of COPD within 6 weeks prior to inclusion.

### Study Device

The Frontier X2 is a chest-worn wearable device designed to monitor physiological parameters in real time. This compact device captures key metrics including HR, BR, HRV, continuous ECG, and physical activity, making it well-suited for continuous health monitoring. The device employs Bluetooth Low Energy technology for data synchronization and is IP67-rated, providing water resistance up to 1.5 m. It also meets international industry standards including International Electrotechnical Commission; International Organization for Standardization; Registration, Evaluation, Authorization and Restriction of Chemicals; Conformité Européenne; and Restriction of Hazardous Substances, ensuring regulatory compliance and durability.

Although initially developed for sports performance monitoring, the Frontier X2 incorporates features with strong relevance for clinical research, such as extended ECG recording and onboard vibration alerts. In this study, the device will be used in passive data collection mode, without real-time alerts being activated. Data are stored locally for up to 24 hours. Given the protocol requirements, participants will be asked to sync data daily via Bluetooth.

Previous studies have demonstrated that the Frontier device has the potential for disease management for people with different chronic diseases [28,29]. Ongoing and future research, including the present study, aims to contribute to the growing body of evidence regarding its accuracy, reliability, and potential applications in chronic disease management. Full specifications and an image of the Frontier X2 can be found at the manufacturer’s website [30].

### Monitoring

The study will monitor both subjective symptom scores and objective physiological metrics to evaluate participants’ health status. Symptom scores will include measures related to appetite, breathing, cough, energy levels, overall wellness, and medication usage, providing insights into fluctuations in COPD symptoms (see Multimedia Appendix 1). Objective physiological parameters, such as HR, BR, ECG, HRV, strain, and daily step count, will be continuously recorded to identify significant changes potentially associated with COPD exacerbations.

Physiological data are collected prospectively, but no real-time clinical monitoring or automated alerts will be used. Data will be reviewed only during scheduled biweekly visits, and participants initiated contact if they reported worsening symptoms, device issues, or unexpected physiological readings. This ensures that the study remains observational and noninterventional. No real-time clinical monitoring or medical decision-making will be performed.

This combined approach, integrating subjective symptom scores with objective physiological data, aims to provide a comprehensive analysis of factors contributing to COPD exacerbations, enabling timely interventions and improved disease management.

### Data Analysis

The data analysis will incorporate both qualitative and quantitative methodologies to ensure a thorough evaluation of the collected data.

#### Qualitative Analysis

Thematic analysis will be undertaken to identify and interpret key themes, categories, and patterns emerging from the qualitative data. Using NVivo software, coding and categorization will facilitate a structured and systematic approach to data interpretation, enabling researchers to gain deeper insights into participants’ experiences and perceptions. This process will provide a foundation for generating hypotheses and addressing the study’s research objectives.

#### Quantitative Analysis

Time-series analysis will be conducted on physiological data to identify patterns and trends over time. Statistical software including SPSS, Minitab, and Python will be used for data processing and analysis. Control chart techniques, particularly the Cumulative Sum (CUSUM) chart, will be applied to evaluate physiological changes before, during, and after COPD exacerbations. The adequacy of the selected time-series models will be assessed through autocorrelation analysis and examination of residual distributions to ensure accurate representation of the underlying data structure.

Physiological parameters, including HR, HRV, and its derived metrics—the root mean square of successive differences, the SD of normal-to-normal intervals, low-frequency power, high-frequency power, and the low-frequency to high-frequency ratio—as well as RR, will be used for quantitative analysis. As this feasibility study is conducted in free-living conditions, it is not possible to fully control contextual factors that may influence HR, RR, or HRV, such as medication changes, intercurrent infections, sleep variability, or changes in daily activity. These factors will therefore be documented during biweekly follow-up visits and reviewed descriptively when interpreting physiological deviations. Analyses will focus on within-participant deviations from each individual’s baseline rather than between-participant comparisons.

The CUSUM chart approach will follow methodologies previously described by Montgomery [31], which enables detection of small, sustained deviations from baseline values in time-series data. For each participant, baseline data will correspond to a stable period with no reported symptom worsening—specifically, the first 7 days of participation. The reference value (k) and decision threshold (h) will be individually calculated based on this baseline period. In accordance with the inclusion criteria, all participants must have been free from any eCOPD events for at least 6 weeks prior to recruitment, supporting the selection of the initial stable days as an appropriate baseline.

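### Activity and sleep changes, which the plan says affect the monitored signals, get only descriptive review although the device records activity, so CUSUM alarms may reflect behaviour

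*Protocol article*

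**What the plan says.** In Quantitative Analysis the protocol article states that in free-living conditions "it is not possible to fully control contextual factors that may influence HR, RR, or HRV", and gives examples: "such as medication changes, intercurrent infections, sleep variability, or changes in daily activity". The consequence it draws is: "These factors will therefore be documented during biweekly follow-up visits and reviewed descriptively when interpreting physiological deviations". It adds one design protection: "Analyses will focus on within-participant deviations" from each person's own baseline, which is the first 7 days of participation.

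The parameters named there for quantitative analysis are heart rate, the heart rate variability metrics and respiratory rate. Elsewhere the article shows that activity is measured. Under Study Device, the Frontier X2 "captures key metrics including HR, BR, HRV, continuous ECG, and physical activity". Under Monitoring, parameters "such as HR, BR, ECG, HRV, strain, and daily step count, will be continuously recorded".

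Quantitative Analysis counts a true detection when the cumulative deviation passes the threshold h in the 7 days before confirmed onset. It counts specificity as no such crossing in stable periods. Data Collection, and the closing paragraph of Quantitative Analysis, say that wear time is recorded but not enforced.

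**The concern.** The reasoning from "it is not possible to fully control contextual factors that may influence HR, RR, or HRV" to descriptive review leaves out a step. Being unable to control activity by design is no reason to leave a recorded measure of it out of the analysis.

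A descriptive note also cannot change the accuracy figures. A crossing of h either happens or it does not, and the plan gives no rule by which a visit note turns a crossing into a non-crossing. Visits every 2 weeks are coarse beside a 7-day window.

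Comparing people with themselves removes stable differences between people, but not changes in one person's activity over time. CUSUM is chosen because it picks up small, sustained deviations, and a sustained change in activity is one of those. With voluntary wear, the mix of hours recorded may also shift, possibly just when someone becomes unwell. At stake are the sensitivity and specificity by which the primary objective, accurate identification of exacerbation onset, would be judged.

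**Working it through.** The document gives no activity effect, no numerical k or h, no aggregation level and no noise level. There is no plan figure to reproduce, so everything below is illustration on assumed inputs.

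**1. Attenuation in a 24 h mean.** Assume that resting heart rate rises 5 bpm, active time carries +25 bpm, and active time falls from 4 to 2 h/day.

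- Change in 24 h mean = 5 − (2 × 25)/24 = 5 − 2.08 = 2.92 bpm.
- Share of the signal lost = 1 − 2.92/5 = 42%.
- Even if all 4 active hours disappeared: 5 − (4 × 25)/24 = 0.83 bpm, still a rise.

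**2. Simulated charts on daily means.** Assumptions: 4000 series per scenario; hourly heart rate = level + 24 h cosine + slope × activity + AR(1) noise (SD 4 bpm, correlation 0.3); 7-day baseline; 7-day test window; k = 0.5 SD, h = 5 SD, alarms in either direction. Slope is bpm per unit of waking activity over 16 waking hours. Slope 6 is paired with a 24 h amplitude of 4 bpm, and slope 10 with 6 bpm. The net shift in the daily mean for a true 4 bpm rise is 4 + slope × activity change × 16/24.

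| Scenario, unadjusted chart | No activity effect | Slope 6 | Slope 10 |
|---|---|---|---|
| No true change, activity unchanged: alarm | 12% | 12% | 12% |
| No true change, activity +30%: alarm | 12% | 38% | 46% |
| No true change, activity −30%: alarm (nearly all downward for slopes 6 and 10) | 11% | 30% | 39% |
| True +4 bpm, activity unchanged: detected | 100% | 98% | 86% |
| True +4 bpm, activity −30%: detected | 100% | 84% (net 2.8 bpm) | 40% (net 2.0 bpm) |
| True +4 bpm, activity −50%: detected | 100% | 60% (net 2.0 bpm) | 10% (net 0.67 bpm) |

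After regression on activity and a 24 h cycle, the stable-week alarm rate is 12–13% in every scenario and detection is about 100%. That is a best case: the simulated activity measure has no error and the fitted model is the true one.

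**3. Hours worn.** Suppose wear moves from 24 h to 16 waking hours centred on the daily peak. The activity term adds slope × (1 − 16/24). The daily cycle adds amplitude × [24/(16π)] × sin(2π/3) = amplitude × 0.4135.

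- Amplitude 4, slope 6: 1.65 + 2.00 = 3.65 bpm.
- Amplitude 6, slope 10: 2.48 + 3.33 = 5.81 bpm.

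Both are about as large as the 4 bpm signal assumed above. With balanced 24 h wear and daily means, time of day matters hardly at all: the alarm rate stays at 12%.

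**4. Limit of adjustment.** On an hourly chart, stable-week alarms are about 98% unadjusted when activity and daily-cycle effects are present. They remain about 90% after adjustment, and are about 86% when neither effect exists. Autocorrelation and the estimated baseline drive this, and activity adjustment does not cure it.

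**The case against.** The strongest reply is that the article never fixes what goes into the chart. A reader might infer that the CUSUM runs on raw all-hours means, but no section says so. Aggregation and pre-processing may lie in the full protocol or analysis plan, and the article does mention time-series models with autocorrelation and residual checks. This stands, and it is why the effect is put as a possibility. It does not remove the point, because the article does commit to one handling of activity and sleep, and that handling is descriptive.

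Three other inferences would go too far. Time of day is not among the factors to be reviewed descriptively; the article does not mention it, and it matters mainly for sub-daily charts or shifting wear hours. Nor do the figures show mean heart rate falling while resting heart rate rises: in the worked example the rise is attenuated, not reversed. And masking or mimicry cannot be stated as a fact, since it vanishes if activity has no effect.

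A substantive objection is that moving less may itself be part of worsening, so adjusting for it can discard useful information. That is correct. It argues for reporting both charts, not for leaving activity out. Finally, this is a 30-person feasibility study that openly acknowledges uncontrolled factors. That bears on how serious the point is, not on whether it holds.

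**Conclusion.** The point holds in a limited form. The plan names activity and sleep as influences on its signals, has activity measurements from the same device, and assigns these influences to fortnightly notes that cannot alter the threshold-based accuracy measures. As a result, a change in activity or in hours worn may mask a true shift or produce a false alarm.

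The size and direction are unknown. Under the assumed inputs, consequences run from none (no activity effect) to a large loss of detection (10% for a 4 bpm rise, with the steeper slope and activity halved). False alarms in a week with 30% more activity run from about 12% to 46%. These ranges depend on the assumed slopes, noise, k, h and daily averaging, and do not estimate what this study will see. The change is worth making before results are reported; it does not call the design into question.

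**What to change.** In Quantitative Analysis, add a pre-specified CUSUM on activity-adjusted input and report its sensitivity and specificity beside those of the unadjusted chart. Either input would serve:

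- one resting or night-time summary per day, taken from low-strain or low-activity periods at whatever resolution the device exports; or
- within-person residuals after regressing each signal on recorded activity and hour of day, fitted on symptom-free days, with those fitting days kept out of the specificity calculation.

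State the aggregation level for both charts, and chart activity as a signal in its own right so that a decline in activity is not lost.

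The cost is mainly analysis work, provided the exports allow it. Monitoring refers to a daily step count, so periods with zero steps may not be identifiable within a day, and the resolution of the strain and activity data is not stated; check this first. Participants with little rest or night wear will contribute less. Adjustment removes whatever information the activity decline carries, which is why the unadjusted chart stays. It does not resolve autocorrelation in an hourly chart, which needs separate handling. The Results section says that analysis runs alongside data collection, so the specification should be dated and should say what had already been examined.
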